## Abstract

**Background:**

Early reperfusion of the occluded coronary artery during acute myocardial infarction is considered crucial for reduction of infarcted mass and recovery of ventricular function. Effective microcirculation and the balance between protective and harmful lymphocytes may have roles in reperfusion injury and may affect final ventricular remodeling.

**Methods/design:**

BATTLE-AMI is an open-label, randomized trial comparing the effects of four therapeutic strategies (rosuvastatin/ticagrelor, rosuvastatin/clopidogrel, simvastatin plus ezetimibe/ticagrelor, or simvastatin plus ezetimibe/clopidogrel) on infarcted mass and left ventricular ejection fraction (LVEF) (blinded endpoints) in patients with ST-segment elevation myocardial infarction submitted to fibrinolytic therapy before coronary angiogram (pharmacoinvasive strategy). All patients (n = 300, 75 per arm) will be followed up for six months. The effects of treatment on subsets of B and T lymphocytes will be determined by flow-cytometry/ELISPOT and will be correlated with the infarcted mass, LVEF, and microcirculation perfusion obtained by cardiac magnetic resonance imaging. The primary hypothesis is that the combined rosuvastatin/ticagrelor therapy will be superior to other therapies (particularly for the comparison with simvastatin plus ezetimibe/clopidogrel) for the achievement of better LVEF at 30 days (primary endpoint) and smaller infarcted mass (secondary endpoint) at 30 days and six months. The trial will also evaluate the improvement in the immune/inflammatory responses mediated by B and T lymphocytes. Omics field (metabolomics and proteomics) will help to understand these responses by molecular events.

**Discussion:**

BATTLE-AMI is aimed to (1) evaluate the role of subsets of lymphocytes on microcirculation improvement and (2) show how the choice of statin/antiplatelet therapy may affect cardiac remodeling after acute myocardial infarction with ST elevation.

**Trial registration:**

ClinicalTrials.gov, NCT02428374. Registered on 28 September 2014.

**Electronic supplementary material:**

The online version of this article (doi:10.1186/s13063-017-2361-1) contains supplementary material, which is available to authorized users.

## Background

An early invasive strategy after fibrinolysis has been proven safe and effective among patients with ST-segment elevation myocardial infarction (STEMI) [1, 2]. However, during acute myocardial infarction (MI), some ligands of the injured tissue are recognized by the innate immune system, triggering the mobilization of inflammatory cells. Yet experimental studies reported that subsets of B lymphocytes may affect the healing process of injured tissue due to the mobilization of monocytes, subsequently affecting ventricular remodeling [3–6]. An increased number of circulating platelets and monocyte microparticles also seems to be related to the severity of the acute MI [7]. Furthermore, it is possible that subsets of lymphocytes and derived microparticles from B or T cells contribute additionally to myocardial injury after reperfusion, due to the release of highly inflammatory interleukins or by affecting thrombus formation [8].

### Subsets of B cells

Experimental studies suggest an important role for B cells in atherogenesis. Initial evidence came from splenectomized ApoE^–/–^ mice developing more severe atherosclerosis compared to sham-treated mice, followed by an impressive attenuation of atherosclerosis after transfer of splenic B cells [9]; however, subsequent studies showed conflicting results and the current understanding suggests a differential role according to B cell subsets [10, 11]. The same theory might be postulated for acute MI. We hypothesized that an increased number of human B CD11b– cells may decrease infarcted mass after reperfusion of an occluded coronary artery. In addition, an increased number of B2 cells, which are considered proatherogenic, may increase the infarcted mass [12]. Other possible players such as highly inflammatory T cells, lymphocyte-derived microparticles, extracellular vesicles, and exosomes may also reach the damaged myocardium, affecting the clotting process [8], oxidative stress [13], and microcirculation [14], thus influencing the recovery of the ischemic tissue [14]. We previously reported that hyperlipidemic individuals treated with rosuvastatin presented better immune responses (higher titers of anti-oxLDL) than those receiving simvastatin/ezetimibe, thus suggesting that the choice of lipid lowering therapy may have possible beneficial role in the acute phase of myocardial infarction [15]. Figure 1 summarizes the study hypothesis regarding B and T lymphocytes.

**Fig. 1 Fig1:**
[figure not shown]
The BATTLE-AMI hypothesis – lymphocytes. After successful coronary reperfusion by a pharmacoinvasive strategy, patients with STEMI might have greater or smaller infarcted mass depending on the balance of B and T lymphocytes. B CD11b– and B memory cells seem to be related to smaller infarcted mass and better left ventricular ejection fraction (LVEF). Conversely, B CD11b + and B-naive cells are possibly related to greater infarcted mass. The role of B and T derived microparticles, extracellular vesicles, or exosomes in the ischemic tissue after coronary reperfusion is not yet established. *PCI* percutaneous coronary intervention

### Microcirculation and the role of ticagrelor/rosuvastatin

In addition to its antiplatelet properties via P2Y12 receptor antagonism, ticagrelor (but not clopidogrel) increases adenosine plasma levels in individuals with acute coronary syndromes [16]. An increase in adenosine concentration following ticagrelor use seems related to the inhibition of the adenosine transporter ENT1 (type 1 equilibrative nucleoside transporter) [17]. This effect of ticagrelor increases coronary blood flow and might be important in the early protection of the ischemic tissue in the acute phase of MI [18].

Rosuvastatin is an active substrate for hydroxymethylglutaryl-Coenzyme A reductase, decreasing the pathway of endogenous cholesterol synthesis. However, pleiotropic effects of statins seem to be mediated by the inhibition of isoprenoids, such as farnesylpyrophosphate and geranylgeranyl pyrophosphate, intermediate substances in the endogenous cholesterol synthesis, required for post-translational changes of small proteins. Consequently, there is a decrease in the intracellular signaling mediated by Rho GTPases. Decrease in Rho protein is followed by increased bioavailability of nitric oxide, promoting vasodilation [19]. Simvastatin is a prodrug that needs metabolization via cytochrome P450, isoenzymes 3A4. Only after this step, the formed metabolites serve as substrates for the hydroxymethylglutaryl CoA reductase, allowing the inhibition of cholesterol synthesis and promoting pleiotropic effects. However, thyenopyridines are also substrates for the same microsomal isoenzymes and some degree of pharmacokinetic interaction can be expected [20, 21]. Thus, another hypothesis of the BATTLE-AMI study is that by acting synergistically, the use of ticagrelor plus rosuvastatin could promote greater improvement in the microcirculation (Fig. 2). Previous studies have shown that the use of high-dose statin decreases biomarkers of myocardial damage in patients undergoing cardiac percutaneous coronary intervention, suggesting early improvement in microcirculation [22, 23].

**Fig. 2 Fig2:**
[figure not shown]
The BATTLE-AMI hypothesis – microcirculation. Microcirculation will be improved by adenosine and nitric oxide. Ticagrelor increases intra- and extracellular levels of adenosine by blocking the adenosine transporter ENT1. Rosuvastatin increases nitric oxide availability through the decrease in the intracellular signaling mediated by Rho GTPases. Decrease in Rho protein is followed by increased bioavailability of nitric oxide, promoting vasodilation. Thus, the synergism between rosuvastatin and ticagrelor will improve the microcirculation of the ischemic myocardium decreasing the final infarcted mass. The absence of effect in adenosine levels following clopidogrel use and the characteristics of simvastatin as a prodrug might have lower beneficial effect on the microcirculation

## Methods

### Study population and randomization

The BATTLE-AMI study (NCT02428374) will include approximately 300 men and women aged > 18 years with documented STEMI submitted to fibrinolytic therapy (tenecteplase, TNK) in the first 6 h of onset of symptoms in public hospitals of São Paulo, Brazil, as part of the SP STEMI treatment network (NCT01791764) [24]. In the network routine, patients are subsequently transferred to a tertiary teaching hospital and undergo systematic early invasive coronary angiography (<24 h, designated as pharmacoinvasive strategy). After obtaining written informed consent in the teaching hospital and before coronary angiography, eligible patients will be randomized using a central computerized system in the first 24 h to one of the four open-label treatment assignments (daily doses) in a 1:1:1:1 ratio: rosuvastatin 20 mg/ticagrelor 180 mg, rosuvastatin 20 mg/clopidogrel 75 mg, simvastatin 40 mg plus ezetimibe 10 mg/ticagrelor 180 mg, or simvastatin 40 mg plus ezetimibe 10 mg/clopidogrel 75 mg. Patients with prior MI, a history of revascularization or stroke, contraindication to study drugs, chronic kidney disease, active liver disease, malignancies, hematological or rheumatic diseases, or showing clinical instability requiring rescue catheterization will be excluded. Other anti-platelet agents or lipid-lowering drugs than those assigned to participants will be prohibited.

Individuals with adverse harmful side effects related to study drugs will be discontinued from trial protocol. Monitoring of adherence to study drugs will be performed by study drug return. Assessment of adherence to study medication and concomitant treatment, as well as patient retention, will be performed at each medical visit and by phone calls. Individuals that discontinue study medication will be followed in the study center according to the scheduled visits of the study.

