### Study design and objectives

The study design of BATTLE-AMI is shown in Fig. 3. The primary objective of the study is to compare the effects of the different antiplatelet/statin therapies in left ventricular ejection fraction (LVEF) obtained by cardiac magnetic resonance imaging (cMRI) 30 days post STEMI. Secondary objectives include the comparison of treatments on infarcted mass and the percentage of participants with LVEF < 40% (by cMRI) at 30 and 180 days of follow-up. In addition, the relation of subsets of B and T lymphocytes with the infarcted mass and LVEF will be examined in samples collected in the first 24 h and at 30 and 180 days post STEMI. Analyses of microbiota, metabolomics, and proteomics will be performed at the same time points aiming at evaluating the lymphocyte differentiation and metabolites related to cMRI parameters. Endothelial progenitor cells and microparticles derived from platelets, endothelium, monocytes, and lymphocytes will be quantified at the same time points and their relationship with cMRI parameters will be evaluated.

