**Fig. 3 Fig3:**
[figure not shown]
The BATTLE-AMI study *flowchart*. After fibrinolytic therapy performed in the 6 h after onset of symptoms, subjects with STEMI will be referred to the hospital for coronary angiography and PCI, if necessary. Those patients admitted to the hospital within 24 h of STEMI will be randomized to one of the four assignments in a 1:1:1:1 ratio (ticagrelor/rosuvastatin, ticagrelor/simvastatin plus ezetimibe, clopidogrel/rosuvastatin, or clopidogrel/simvastatin plus ezetimibe). Blood, urine, and feces samples will be collected at baseline, 30 days, and 180 days for metabolomics, proteomics, microbiota, and flow-cytometry studies. cMRI studies will be performed during peri-hospitalization period and at 30 and 180 days

Our main hypothesis is that rosuvastatin/ticagrelor will be superior than simvastatin plus ezetimibe/clopidogrel, for the cMR parameters. Additionally, the pilot study indicated that the ezetimibe/clopidogrel was similar to simvastatin plus ezetimibe/ticagrelor and rosuvastatin/clopidogrel combinations regarding the primary endpoint and we decided to compare those other groups (rosuvastatin/clopidogrel and simvastatin plus ezetimibe/ticagrelor) to explore possible mechanisms for the primary and secondary objectives.

Thereafter, our sample size derivation was done considering that rosuvastatin/ticagrelor will improve mean cMRI LVEF by 6% compared to each of the other three groups, assuming a 13% dropout rate. The alpha level fixed in 0.05/3 (1.67%) was considered to adjust the global alpha error in 5% using Dunnett’s test approach (many-to-one comparisons).

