**Fig. 4 Fig4:**
[figure not shown]
Schedule of enrolment, interventions, and assessments. *TICA* ticagrelor, *RSV* rosuvastatin, *Sinva* simvastatin, *CLO* clopidogrel, *EZE* ezetimibe, *cMRI* cardiac magnetic resonance imaging

This is an open label study, with outcome assessors and data analysts blinded to treatment assignment.

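### Two follow-up rules conflict for patients who stop because of drug-related side effects, so their 30-day cMRI, the primary outcome, could be lost

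*Protocol article*

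**What the plan says.** Protocol article, Methods, Study population and randomization, second paragraph, gives two rules.

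- Its opening sentence: "Individuals with adverse harmful side effects related to study drugs will be discontinued from trial protocol".
- Its closing sentence: "Individuals that discontinue study medication will be followed in the study center according to the scheduled visits of the study".

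The Abstract (Methods/design) adds: "All patients (n = 300, 75 per arm) will be followed up for six months". The Fig. 3 legend places cMRI in the peri-hospital period and at 30 and 180 days, with no exception for patients off study drug.

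The primary objective, under Study design and objectives, concerns "left ventricular ejection fraction (LVEF) obtained by cardiac magnetic resonance imaging (cMRI) 30 days post STEMI". On blinding, Data collection and analyses says: "This is an open label study, with outcome assessors and data analysts blinded to treatment assignment". The sample size rests on the expectation that "rosuvastatin/ticagrelor will improve mean cMRI LVEF by 6% compared to each of the other three groups", and its only provision for loss is the phrase "assuming a 13% dropout rate".

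**The concern.** The two rules overlap on one group: patients who stop study drug because of a side effect attributed to it. The first rule can be read as taking them out of the trial. The second keeps them in follow-up. The article does not say which prevails, so sites could act differently.

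If the first rule is applied as removal before day 30, the patient has no primary outcome. The trigger arises after randomisation, depends on the assigned drugs, and is a causal judgement made in an open-label trial. Blinded readers cannot correct for a scan that was never acquired, and no later analysis can recover it. The comparison would then be among patients who tolerated their assigned drugs, not among all those randomised. The 13% allowance protects the number of evaluable patients. It does not protect the comparability of the arms.

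**Working it through.** **Step 1: the text.** Two readings of the opening sentence are possible.

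- *Off protocol treatment.* The closing sentence then applies, the patient keeps the scheduled visits, and no scan is lost. The Abstract's six-month follow-up of all patients and the Fig. 3 schedule support this reading.
- *Out of the trial.* Visits and cMRI end. The wording lends itself to this, because the paragraph calls the treatments study drugs or study medication wherever it means them, and uses *trial protocol* only here.

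Nothing printed decides between the two.

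**Step 2: the plan's own figure.** There are 75 patients per arm and 13% dropout. Evaluable: 75 × (1 − 0.13) = 65.25. In reverse, 65 / 0.87 = 74.7, which rounds up to 75, so the dropout step is consistent. SD, power and sidedness are not printed in the article. With an assumed SD of 10.5, 80% power and two-sided alpha 0.05/3, n = 2 × (10.5/6)² × (2.394 + 0.842)² = 64.1, which rounds up to 65 and becomes 75 after dropout. This agrees with the plan, but the SD was chosen to fit, so it is not an independent reproduction. The 6% is read as 6 LVEF points.

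**Step 3: the bias formula.** Let a share q of an arm be removed, with mean LVEF d points below the retained mean m. The mean of the whole arm is (1 − q)m + q(m − d) = m − qd, so the retained mean is too high by qd. The bias in a difference between arms 1 and 2 is q₁d₁ − q₂d₂. With a common deficit d this is (q₁ − q₂) × d, in favour of the arm that loses more.

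**Step 4: the numbers.** All shares and deficits are assumed, because the documents give none.

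| Removed, arm 1 v arm 2 | d (points) | Bias (points) | Share of 6 points |
|---|---|---|---|
| 13% v 13% | any, equal | 0 | 0% |
| 10% v 5% | 3 | 0.05 × 3 = 0.15 | 2.5% |
| 10% v 5% | 10 | 0.05 × 10 = 0.50 | 8.3% |
| 13% v 5% | 3 | 0.08 × 3 = 0.24 | 4.0% |
| 13% v 5% | 10 | 0.08 × 10 = 0.80 | 13.3% |
| 20% v 6% (stress case) | 10 | 0.14 × 10 = 1.40 | 23.3% |

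**Step 5: effect on the error rate.** Take SD 10.5 and a nominal two-sided level of 0.0167 per comparison. For 13% v 5%, the retained numbers are 65.25 and 71.25, and the standard error is 10.5 × √(1/65.25 + 1/71.25) = 1.80. Under no true difference, the rejection probability is 0.019 at d = 5 (bias 0.4) and 0.028 at d = 10 (bias 0.8). In the stress case it is 0.052.

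**Step 6: effect on power.** If side-effect removals came on top of the 13% (assumed extra 5% or 10%), evaluable patients per arm would fall from 65.25 to 61.5 or 57.75. At SD 10.5, power would fall from 80.8% to 78.1% or 75.1%.

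**The case against.** The strongest reply is that the paragraph can be read without conflict. Discontinuation from the protocol may mean discontinuation of protocol treatment. The closing sentence makes no exception for side effects, the Abstract promises six months of follow-up for all, and no sentence says that a scan is skipped. This stands as far as it goes: loss of the primary outcome is a possible consequence of the wording, not something the plan prescribes. It does not remove the ambiguity, because a site could reasonably take the opening sentence at its word.

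A reader might infer that the primary outcome will be lost selectively by arm. The documents do not support that. It would need removals before day 30, removal rates or prognosis that differ between arms, and a link between side effects and LVEF. The article gives no figure for any of these.

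A reader might also set the shift in one arm's mean against the target effect: 0.13 × 10 = 1.3 points, or 22% of 6. That compares a one-arm shift with a between-arm difference. It holds only if 13% are removed from one arm and none from the other, and it assigns the plan's whole dropout allowance to side effects.

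Finally, the analysis population is commonly left to the full protocol or SAP, which is not shown, and its absence from the article is no fault. The point here is narrower: it concerns a data-collection rule that the article prints in two unreconciled forms.

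**Conclusion.** The point holds as an unreconciled pair of rules with a conditional risk to the primary endpoint. Under one reading nothing is lost. Under the other, the 30-day LVEF could be missing for a treatment-related reason judged with treatment known.

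The resulting bias is zero if removal and deficit are equal across arms. It is about 0.15 to 0.8 points, or 2.5% to 13% of the 6-point target, under assumed removal of 10% v 5% or 13% v 5% and a common deficit of 3 to 10 points. Larger values need more extreme assumptions. The error rates and power losses also rest on an assumed SD of 10.5.

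The expected size is modest and uncertain. The ambiguity is still worth removing, because it decides who contributes the primary outcome and a missed scan cannot be replaced.

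**What to change.** Reconcile the two sentences under Study population and randomization. State that patients discontinued for side effects remain in scheduled follow-up, including the 30- and 180-day cMRI, unless they withdraw consent, and that they stay in their randomised arm. If the full protocol or SAP already says so, the article's wording only needs to be aligned with it. This takes no position on when or whether study drug is stopped. What the opening sentence requires for treatment is for the sponsor to state.

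The cost is a short amendment and an instruction to sites. The Fig. 3 legend already schedules the scans, so no new assessment is added. Trial status reports that recruitment began in May 2015 and is ongoing, so the change protects future scans but cannot recover any already missed.

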### Study design and objectives

The study design of BATTLE-AMI is shown in Fig. 3. The primary objective of the study is to compare the effects of the different antiplatelet/statin therapies in left ventricular ejection fraction (LVEF) obtained by cardiac magnetic resonance imaging (cMRI) 30 days post STEMI. Secondary objectives include the comparison of treatments on infarcted mass and the percentage of participants with LVEF < 40% (by cMRI) at 30 and 180 days of follow-up. In addition, the relation of subsets of B and T lymphocytes with the infarcted mass and LVEF will be examined in samples collected in the first 24 h and at 30 and 180 days post STEMI. Analyses of microbiota, metabolomics, and proteomics will be performed at the same time points aiming at evaluating the lymphocyte differentiation and metabolites related to cMRI parameters. Endothelial progenitor cells and microparticles derived from platelets, endothelium, monocytes, and lymphocytes will be quantified at the same time points and their relationship with cMRI parameters will be evaluated.

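### At 180 days the only LVEF comparison between arms that the article names is the percentage below 40%, which has clearly less power than the mean LVEF the same scan provides

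*Protocol article*

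**What the plan says.** Under Study design and objectives, the primary objective is the comparison of LVEF by cardiac MRI 30 days after STEMI. The secondary treatment comparisons listed there are infarcted mass and "the percentage of participants with LVEF < 40% (by cMRI) at 30 and 180 days of follow-up". The abstract (Methods/design) agrees: it attaches better LVEF to 30 days, and attaches the six-month time point to infarcted mass only.

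The 180-day scan is part of the schedule. According to the Fig. 3 caption, "cMRI studies will be performed during peri-hospitalization period and at 30 and 180 days". Under Cardiac magnetic resonance images, cine images give LVEF, volumes and mass, and each study is read by two independent blinded readers. One aim in the abstract's Discussion is to "show how the choice of statin/antiplatelet therapy may affect cardiac remodeling".

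LVEF also appears in the analyses of lymphocyte subsets and, as one of the cardiac MRI parameters, in those of other markers. Those are associations, not comparisons between arms.

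**The concern.** The article is not silent on the form of the 180-day LVEF comparison. It names a threshold. Dichotomising a continuous measurement treats LVEF of 41% and 65% as the same result, and 39% and 41% as opposite results. The comparison then depends on how many patients lie near 40%.

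At 30 days this does little harm, because mean LVEF is primary there. At 180 days no such comparison stands beside it. If a difference of the size the trial was designed to detect persists to six months, the named LVEF comparison is less likely to show it than the mean would be. A result on mean LVEF at 180 days could not be traced to an endpoint named in this article.

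**Working it through.** **1. What is named for comparison between arms**

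| Measure | 30 days | 180 days |
|---|---|---|
| Mean LVEF | primary | not named |
| Percentage with LVEF < 40% | secondary | secondary |
| Infarcted mass | secondary | secondary |

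**2. Inputs from the article**
- Size: "All patients (n = 300, 75 per arm) will be followed up for six months", allocated 1:1:1:1.
- Effect: "rosuvastatin/ticagrelor will improve mean cMRI LVEF by 6% compared to each of the other three groups", read here as 6 LVEF points.
- Dropout: "assuming a 13% dropout rate", so 75 × 0.87 = 65.25, or 65 evaluable per arm.
- Alpha per comparison: 0.05/3 = 0.0167.

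**Assumptions, not in the article:** two-sided testing (z = 2.394), normal LVEF with a common SD, the same 6-point difference at 180 days, the SD, and the comparator mean.

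**3. Reproducing the stated sample size**

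n per arm = 2 × SD² × (2.394 + 0.842)² / 6².

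With SD 10.5 and 80% power: 2 × 110.25 × 10.47 / 36 = 64.1, rounded up to 65. Then 65 / 0.87 = 74.7, rounded up to 75 per arm and 300 in total. This shows that SD 10.5 with 80% power fits the stated size. It does not show that these were the values used: 65 per arm fits 90% power with SD 9.3 equally well.

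**4. Power for mean LVEF, 65 per arm, SD 10.5**

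Standard error = 10.5 × √(2/65) = 1.842. Power = Φ(6/1.842 − 2.394) = Φ(0.864) = 0.81. With the t distribution it is 0.80.

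**5. Power for the percentage below 40%**

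The proportion below 40% in an arm is Φ((40 − mean)/SD). Power = Φ[(√n × |p₁ − p₂| − 2.394 × √(2p̄(1 − p̄))) / √(p₁(1 − p₁) + p₂(1 − p₂))].

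Worked case, means 50 and 56: p₁ = Φ(−10/10.5) = 0.170 and p₂ = Φ(−16/10.5) = 0.064. The difference is 0.1067, and √65 × 0.1067 = 0.860. The two square roots are 0.4548 and 0.4485. Power = Φ((0.860 − 2.394 × 0.4548)/0.4485) = Φ(−0.51) = 0.305.

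| Comparator mean | Below 40%: comparator v rosuvastatin/ticagrelor | Power | Share of 81% lost | Evaluable per arm to match 81% |
|---|---|---|---|---|
| 42 | 42.4% v 22.3% | 52% | 35% | 114 |
| 45 | 31.7% v 14.7% | 46% | 43% | 131 |
| 48 | 22.3% v 9.1% | 37% | 54% | 161 |
| 50 | 17.0% v 6.4% | 31% | 62% | 192 |
| 52 | 12.7% v 4.3% | 24% | 70% | 237 |
| 55 | 7.7% v 2.3% | 16% | 80% | 345 |

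The trial expects 65 evaluable per arm.

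**6. Sensitivity**
- SD 8 to 12 and comparator mean 42 to 55, alpha 0.0167: mean LVEF has 68% to 97% power and the cut has 10% to 76%. The efficiency of the cut relative to the mean is 0.07 to 0.59.
- Alpha 0.05, SD 10.5: 90% for mean LVEF against 69%, 47% and 29% at comparator means 42, 50 and 55.
- The cut has less power than the mean in every scenario tried.

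**The case against.** The strongest reply is that this is a condensed article. Its list of secondary objectives is introduced in terms that need not be exhaustive, and the main hypothesis refers to cardiac MRI parameters in general without a time point. A continuous 180-day LVEF analysis may therefore stand in the full protocol or SAP, which are not shown. This stands as a limit: the documents do not show that no such analysis is planned. It does not remove the point, because the article does state the form of the 180-day LVEF comparison and chooses the weaker one, and the abstract ties mean LVEF to 30 days.

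It is also fair to say that LVEF below 40% is a readable clinical measure, that secondary endpoints need not be powered, and that the article claims no power for this one. That is a reason to keep the measure, not to make it the only LVEF comparison named at six months.

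A reader might infer three stronger things that the documents do not support:
- *Most of the power of the 180-day scan is lost.* Infarcted mass from the same scan is a named 180-day comparison, and the scan also feeds the association analyses. Only the LVEF comparison is affected. Even there, at SD 10.5, the loss exceeds half only from a comparator mean of about 47 upward.
- *A real 6-point difference would probably be reported as not significant.* This holds in many scenarios but not all. At comparator mean 42, power is 52% with SD 10.5 and 76% with SD 8.
- *The remodeling aim rests mainly on the 180-day scan.* The article does not say so. Its Discussion ties the expected influence of lymphocytes to final infarcted mass and to LVEF at 30 days.

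**Conclusion.** The point holds as a stated, less efficient choice of analysis, not as an error or a contradiction. Mean LVEF is named for comparison at 30 days only. At 180 days the article names a cut at 40%, although the blinded reading already produces the continuous value.

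At SD 10.5 the loss runs from about a third of the power (comparator mean 42) to about four-fifths (comparator mean 55). These figures rest on an SD, a comparator mean and a 180-day difference that the article does not give. They also apply the sample-size alpha to a secondary endpoint, which the article does not specify. The direction of the result does not depend on these values within the ranges tried, but its size does. The primary analysis and the sample size are unaffected.

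**What to change.** Name mean LVEF at 180 days as a secondary treatment comparison, using the same contrasts of rosuvastatin/ticagrelor with each of the other three arms. Optionally, estimate it in one repeated-measures model with the 30-day value, so that patients with one missing scan still contribute. Keep the percentage with LVEF below 40% as a supportive clinical summary. If the full protocol or SAP already contains this comparison, a line saying so is enough.

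The cost is wording in the endpoint list and analysis plan, and one more secondary comparison to report. No extra patients, scans or readers are needed.
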